#### Outcome measures

Primary outcome measure for economic evaluation (within-trial CUA) would be sepsis episodes and related deaths averted in the intervention arm as compared with the placebo arm, which translates to gain in life years and DALYs averted as long-term measure.

Data requirements: data requirements for economic evaluation are tabulated in table 1.

**Table 1 T1:** Data requirements for economic evaluation

Data type	Significance for the model	Source of data
Demographic	Estimate the baseline parameters Estimate target population	Primary data collection; Census of India
Treatment effects and incidence of adverse events	Efficacy and safety parameters Cost estimation Outcome assessment	RCT Database
Background mortality data	Estimate natural mortality in the target population	SRS, Published literature
Utilities	Estimate DALY as long-term outcome measure	Global Burden of Diseases estimates (2011)
Resource use and price data	Cost estimation	Primary data collection; NHSC—Prinja *et al*
Epidemiological data	Estimate baseline risk of clinical events	Published literature; Primary data collection (Control arm of the RCT)

NHSCD, National Health Systems Costing Database; RCT, randomised control trial; SRS, Sample Registration System.

Utility data would allow incorporating the relative impact of a health technology (ie, probiotics) on the neonatal health outcomes in terms of disability burden. This will be estimated as DALYs averted. Utility data would be obtained from Global disease burden estimates 2017. Cost data are important drivers of cost-effectiveness, as they quantify the resource consumption associated with the use of health technologies.

Decision-analytic model would be populated with cost data from the societal perspective: direct medical and non-medical cost borne by patients; and direct medical cost borne by the healthcare system. A National Health Systems Costing Database (NHSCD) to estimate healthcare system’s costs in India has been developed.^12^ Data on patient’s out-of-pocket (OOP) expenses would be collected during the conduct of the RCT as primary data.

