### Study details

Total of 6144 (N) new born babies with LBW would be screened for eligibility and randomly assigned to probiotic (n=3072) or placebo (n=3072) groups and administered 1 mL of the probiotic suspension daily for 30 days. The study would use Interactive Web Respons System (IWRS) for the purpose of stratified randomisation by birth weight, sex and study site. Trained field workers will make home visits daily for first 7 days and thereafter three times in a week till day 30 of the follow-up period to ensure and monitor adherence to the intervention and collect morbidity information. After the 30-day intervention period, home visitation will continue at weekly interval till day 60 of life. During home visitation as per schedule, trained fieldworkers would screen infants for symptoms/signs of possible serious bacterial infection (PSBI)/clinical illness/clinical severe infection. To record the adverse event (AE)/serious adverse event (SAE) (if any), continuous monitoring and reporting of ongoing medical conditions, signs and symptoms will be conducted by field worker during their scheduled follow-up home visits using software on handheld device during the 2-month period of follow-up. Presence of any danger signs would be evaluated, and need for referral would be assessed: if a child is found to have any symptoms/signs from the list, the field worker will accompany the infant to facility for examination by study physician (referral). The study physician would examine the infant again for symptoms/signs of PSBI/clinical illness/clinical severe infection and confirm the diagnosis. Investigations such as blood culture, sepsis screen would be performed for suspected cases of neonatal sepsis by study physician. If required, the infant would be hospitalised for treatment. Data on outcomes, lab investigation and treatment during clinical management of the sick, new born will be collected and SAEs will be reported as per regulatory guidelines. Blood culture isolates will be shipped by site to microbiology lab at All India Institute of Medical Sciences, New Delhi for quality assurance purpose.

The study will be implemented according to MRC guidelines for management of global health trials and will be governed by a Trial Steering Committee and a Data Management Committee.

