### Costing

In the current study, cost of Vivomix (intervention), cost of routine home-based postnatal care, cost of illness management, drug costs, vitamin/mineral supplement costs, laboratory investigation charges, doctor consultation and bed charges are categorised as direct medical costs and the informal payments and travel are categorised as the direct non-medical costs. Loss of wages of parents and other caregivers due to absenteeism from work and is categorised as indirect costs. Neonatal sepsis episodes are treated in in-patient (IP) setting; therefore, respondents (parents and caregivers) will be interviewed to collect information on days they were absent from work due to hospital stay for treatment. After hospital discharge, follow-up with parents and caregivers to assess any effect on their productivity at work is beyond the scope of data collection in the present study. All costs related data would be collected from all six study sites in a representative manner.

*Sample size (costing):* we calculated the sample size to estimate the mean OOP expenditures among the neonates with illness (here PSBI). A power of 80% and 5% level of significance was assumed for sample size calculation. The baseline estimate for OOP among neonates with PSBI was accessed from an Indian study.^1^ Assuming a mean OOP of ₹2003 (SD: ₹3517) for neonates with PSBI and an error margin of 7.5%, the minimum sample size computed to estimate the OOP was 1998. In view of high variability in the OOP data, the error margin of 7.5% was considered appropriate for sample size calculation. The data on OOP will be captured for a subsample, that is, 1998 neonates, out of total sample recruited in the study. At each of the six subjects’ recruitment sites, data would be collected on 333 subjects for this substudy. The OOP data will be collected irrespective of status of neonates belonging to two study arms. The formula used for sample size calculation is given below: n=Z21_1-a/2_ s2 d^2^

$$n=\frac{Z_{1-a}^{2}/2S^{2}}{d^{2}}$$

Where

n=minimum estimated sample size.

Z^2^_1-a_= table value from standard normal distribution.

s^2^=SD of outcome variable in study population.

d^2 =^ error margin (or absolute precision).

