*Data collection and estimation of costs:* data collection for the current study would be completed in 1 year duration from September 2022 to August 2023 (to cover any variation with seasonality). Data on OOP expenditures will be collected on a subsample of 333 subjects drawn from the total trial population in a representative manner.

Sociodemographic data on education, occupation of parents of enrolled children is being collected on study forms. Parents would be asked about any illness during the study period and any expenditures on account of care seeking, visits to facilities, hospitalisation and treatment. Direct medical and non-medical costs due to neonatal sepsis would be ascertained in all 333 subjects at the six study sites. Data on OOP expenditure in public or private health facilities would be elicited.

Intervention cost would be facilitated through primary data collection and the programme budgetary records. The cost of treatment for neonatal sepsis and related diseases at secondary and tertiary level will be ascertained from the NHSCD^15 16^ and published literature in Indian context.^12^ These sources provide estimates on cost per IP admission, cost of intensive care unit admission, cost per out-patient consultation accounting for resources consumed for service provision such as medical (drugs, diagnostics, procedural, hospital charges) and non-medical (transportation, boarding and lodging). In addition, cost related to Information Education and Communication (IEC) material, monitoring and supervision and other administrative costs will also be estimated. Assumptions made in the study protocol are provided in table 2.

**Table 2 T2:** Key methods and assumptions for economic evaluation

Component	Consideration/approach	Justification
Intervention	Vivomixx (eight strain probiotics) + sepsis management Dose: 1 mL/day (10 billion CFU/mL) for 30 days Intervention delivery: under the supervision of study staff (field worker)	Effectiveness of Vivomixx for preventing neonatal sepsis is being assessed under trial
Comparator	Placebo	Effectiveness of Vivomixx is being assessed under trial against placebo Use of antibiotic is routine practice for sepsis management.
Target population	High-risk LBW neonates (both pre-term and small for-date babies)	Most vulnerable high-risk population with high morbidity and mortality

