Objective	To assess the incremental cost per DALY averted with use of probiotics for prevention of neonatal sepsis compared the placebo	Besides effectiveness, evidence on cost-effectiveness is mandatory for adoption of treatment/intervention under public policy
Target Audience/policy use	National Health Mission (NHM) Any other	This intervention is to be implemented under RMNCH programme
Method	Both model and trial based	Short –term outcome estimates will be used for trial Use of model-based CEA will enable us to assess long-term outcomes (and sub-group analysis)
Perspective	Societal perspective	OOP burden associated with sepsis management among LBW neonates
Analytic horizon	6 months	To model long-term outcomes (DALYs)
Costs	Health system costs (Vivomixx cost; Cost of routine HBPNC care; cost of illness management etc.) OOP expenditures (doctor’s consultation; bed charges; drug costs; vitamin/mineral supplement costs; investigations; procedures; informal payments; travel cost etc.	Both health system and patients’ costs as per societal perspective considered for CEA
Outcomes	Sepsis episodes and deaths averted DALYs Hospitalisation averted Life years gained	In line with study design (cost-effectiveness/cost-utility analysis)
Discount rate	3%	As per Indian reference case

CEA, Cost Effectiveness Analysis; DALYs, disability-adjusted life years; HBPNC, home-based postnatal care; LBW, low-birth weight; OOP, out-of-pocket.

Total cost will be comprised of cost of intervention, cost of management of sepsis and associated complications and patient costs as OOP. Similarly, total cost in the control arm will be estimated in the absence of intervention. Annual discount rate of 3% will be used wherever applicable. In the present study, both model-based approach as well as trial data would be used. Data management and analysis will be done using MS-Excel.

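### The scope of costs is contradictory: the total-cost sum counts management of sepsis only, other text covers PSBI, any illness and adverse events, and lost work is collected only for hospital stays

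*Protocol article*

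**What the plan says.** All references are to the protocol article.

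- **Total cost** (Costing, text after Table 2): "Total cost will be comprised of cost of intervention, cost of management of sepsis and associated complications and patient costs as OOP". Control-arm cost is to be built in the same way without the intervention.
- **Cost collection** (Costing, data collection and estimation of costs): "Parents would be asked about any illness during the study period", together with any spending on care. The next statement on scope is narrower: "Direct medical and non-medical costs due to neonatal sepsis would be ascertained".
- **Adverse events** (Outcome measures, Table 1): the row "Treatment effects and incidence of adverse events" lists cost estimation among its uses, with the RCT database as source.
- **Outcomes** (Primary outcomes): sepsis and PSBI are both listed.
- **Lost work** (Costing): the premise is "Neonatal sepsis episodes are treated in in-patient (IP) setting". Caregivers therefore "will be interviewed to collect information on days they were absent from work due to hospital stay for treatment". After discharge, "follow-up with parents and caregivers to assess any effect on their productivity at work is beyond the scope of data collection".
- **Admission** (Study details): after the study physician's examination and tests, "If required, the infant would be hospitalised for treatment".
- **Perspective** (Abstract and Table 2): societal.

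**The concern.** Incremental cost is the numerator of the cost-effectiveness ratio, so the two arms must be costed over a defined set of events. Here that set changes from place to place. Two analysts working from this text could compute different numerators from the same trial data.

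The narrow version has a further weakness. Whether an episode's health-system cost counts would depend on culture and sepsis-screen results that arrive after the consultation, the tests and possibly the admission have been paid for. If the product prevents illness that is treated as infection but never meets the sepsis definition, that saving is lost. If it causes other illness, that cost is lost.

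Under a societal perspective, work lost for care without admission also belongs in the comparison, and the interview as described does not ask about it.

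**Working it through.** The article gives no figure on this point to reproduce. The one computed number in the Costing section, the OOP sample of 1998, matters here only because it is based on neonates with PSBI (mean ₹2003, SD ₹3517). Its arithmetic is a separate matter. The check sets the statements side by side.

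**1. Statements on scope**

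| Narrow: sepsis | Wider |
|---|---|
| Abstract, Methods and analysis: direct costs are those of neonatal sepsis and its treatment | Same paragraph: treatment costs are also sought for associated conditions |
| Costing, data collection: costs due to sepsis are ascertained | Same section: parents are asked about any illness; unit costs cover sepsis and related diseases |
| Costing, after Table 2: the total-cost sum | Costing, first paragraph, and Table 2, Costs row: illness management, with no cause named |
| Table 2, Perspective row: justified by the OOP burden of managing sepsis | Costing, sample size: OOP sized on PSBI |
| | Table 1: adverse events feed cost estimation |

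The benefit side is also wide. Effectiveness assessment expects fewer admissions for infectious disease of any kind, and the Outcomes row of Table 2 lists hospitalisation averted without limiting it to sepsis.

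**2. One infant traced through the rules**

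Take an enrolled infant aged 5 days with fever confirmed by the study physician, a sterile culture and one abnormal screen marker.

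- Sepsis: not met. The definition needs an isolate or at least two abnormal markers.
- PSBI: met, on one sign.
- Resources under Study details: accompanied referral, physician examination, culture and sepsis screen where sepsis is suspected, and admission where needed.
- Household spending: inside the sum under the any-illness question, outside it under the costs-due-to-sepsis sentence.
- Health-system cost: outside the sum read literally, because this is neither sepsis nor a complication of sepsis. It is inside if illness management or related diseases governs.

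**3. What the difference does to the numerator**

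Write each term as the difference in mean cost per infant, probiotic minus placebo: I for intervention, Hs for health-system cost of sepsis and complications, Hp for health-system cost of PSBI not meeting sepsis, Ha for health-system cost of adverse events, O for OOP, W for lost wages.

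- Literal sum: I + Hs + O
- Full sum: I + Hs + Hp + Ha + O + W
- Difference, full minus literal: Hp + Ha + W

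The ratio shifts by (Hp + Ha + W) divided by DALYs averted. If the product reduces non-sepsis PSBI, Hp is negative and the literal sum overstates incremental cost. If it causes adverse events that use care, Ha is positive and the literal sum understates it. The net direction is unknown.

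**4. Lost work**

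The restriction to hospital stay rests on sepsis being treated in hospital. Study details makes admission conditional for infants referred with PSBI signs, and the cited costing sources include a cost per out-patient consultation. Work lost for care without admission is therefore not collected.

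Separately, Costing defines caregivers' lost wages as indirect costs. The total-cost sum does not name them, the OOP items in Table 2 do not list them (that list is open-ended), and the list of societal costs under Outcome measures contains direct costs only.

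**The case against.** The strongest reply is that one summary sentence is being read as an exclusive rule. Illness management is listed as a cost in two places, unit costs extend to related diseases, and Table 1 is a positive plan to use adverse events in costing. PSBI could fall under any of these. Figure 2, the decision tree, is not available here and may contain PSBI or out-patient branches. The stated objective is prevention of sepsis, so costing the modelled condition is a defensible choice. The hospital-stay limit on lost work is disclosed, and it is consistent for sepsis to be treated in hospital while other referred infants are not admitted.

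Much of this stands, and it rules out two stronger readings that a reader might reach:

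- **That the plan limits all management cost to sepsis, or leaves the effect on total illness unvalued.** The documents do not support this. Parents are asked about any illness, OOP enters the total, and several statements on health-system cost are wider than sepsis.
- **That a stated share of infection episodes goes uncosted.** The article gives no ratio of PSBI to sepsis. Any such share would only restate an assumed ratio, and it would count episodes rather than costs.

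The reply does not remove the contradiction. The only sentence that says how total cost is assembled takes the narrow side for management cost, and nothing says which statement prevails. A condensed article may leave itemised costing to a fuller document, but what it does state should agree. Nor does the sepsis objective explain why lost work for a non-admitted PSBI infant is left out when that infant's OOP cost is sought.

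**Conclusion.** The cost scope is internally contradictory and should be reconciled before analysis. Read literally, household cost covers any illness while health-system management cost covers sepsis and its complications only, so savings on non-sepsis PSBI, or costs of adverse events, can drop out of the incremental cost. Work lost without admission is not collected, and wage losses are not named in the sum although the article defines them as a cost category.

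The size cannot be given: it equals Hp + Ha + W per infant, and the documents contain no input for any of the three terms. The conclusion rests on two assumptions. The first is that the total-cost sentence is the operative rule. The second is that some infants have PSBI without meeting the sepsis definition, which the definitions allow and the conditional admission step anticipates. This is a point that should be corrected; it does not show that the evaluation as a whole is invalid.

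**What to change.** 1. Restate the rule. Total cost per infant, by arm, is intervention cost plus health-system and household cost, including lost wages, of (a) sepsis and its complications, (b) PSBI not meeting the sepsis definition, and (c) the adverse events and SAEs that Table 1 assigns to costing, over the trial follow-up. Report sepsis-specific cost as a breakdown.
2. Say which adverse events fall under (c). Costing every unrelated event is debatable and is not required by this point.
3. Bring the Abstract, the costs-due-to-sepsis sentence and Tables 1 and 2 into line with that rule. Use the same scope when the model carries costs to the 6-month horizon.
4. Ask caregivers about work days lost for any care-seeking, out-patient visits included. If interviews have closed, state the gap as a limitation of the societal perspective.

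Cost: mostly wording, one broader interview item and a few extra unit costs. Morbidity, treatment and SAE data are already collected under Study details. The downside is a somewhat noisier cost estimate than a sepsis-only one; the sepsis breakdown keeps the narrower figure available.

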#### Other analyses

Uncertainty analyses, budget impact analysis, stakeholder analysis would be included.

#### Uncertainty analysis

Both deterministic and probabilistic sensitivity analysis (PSA) will be undertaken to address the effect of uncertainties present in analysis. For PSA, all the parameter values will be varied within a plausible range. Based on nature of parameter, an appropriate probabilistic distribution will be assigned such as beta distribution for risk and utility parameters, gamma distribution for cost parameters, uniform distribution for demographic parameters, etc. The results under PSA will be simulated 999 times to report a 95% CI for ICERs.

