## Introduction

There is progress towards attaining the third Sustainable Development Goal (SDG) of under-five (U5) mortality of 25 per 1000 live births by 2030, in India. Neonatal mortality rate is the most important contributing factor of the U5 mortality.^1 2^ Further decline in neonatal mortality may require newer interventions for prevention or treatment of neonatal infections like meningitis, pneumonia, septicaemia that result in more than a quarter of the 1 million neonatal deaths every year in India.^2^

The ProSPoNS trial^3^ proposes to evaluate the role of probiotics in prevention of neonatal infections (sepsis) among the vulnerable group of low-birth weight infants contributing the highest rates of morbidity and mortality. A larger sample size and precise outcome measures differentiate this trial from the earlier conducted pilot study that showcased a 21% non-significant decline in morbidity due to neonatal sepsis in the intervention arm. Considering the 30% prevalence of low-birth weight (LBW) in India and 30% mortality due to neonatal sepsis, even a small decline in the incidence of sepsis would translate to a large number of new born lives saved.^3^

If the intervention is proven to be efficacious, it would be important to know whether it is also a cost-effective intervention. There are few examples in the literature where economic evaluations have been conducted on other effective interventions to prevent neonatal sepsis.^4 5^ It cannot be overemphasised that along with clinical effectiveness of interventions, an estimate of economic effectiveness either in terms of costs or utilities (disability-adjusted life years; DALYs and Quality adjusted life years; QALYs) is required to make correct choices about their inclusion in public health programmes. This is of immense importance in presence of multiple competitive options where prioritisation is needed.

Ranjeva *et al*^6^ have quantified the scope of the public health and economic burden of neonatal sepsis in Sub-Saharan Africa. However, evidence on the health economics aspect of neonatal sepsis prevention effect of probiotics has not been ascertained so far. We propose to evaluate the cost utility of probiotic intervention for prevention of neonatal sepsis within the ProSPoNS trial.

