A health economic evaluation using CUA design will be conducted within the ProSPoNS trial. The results would provide the incremental costs and health gains of the probiotic intervention in absence of any prevention modality being implemented or available. Decision-analytical modelling using the trial results would be extrapolated to the target population and time horizon to inform policy on the potential for incremental costs offsets attributable to prevention of morbidity with the proposed intervention. The CUA will use the present results as cost per case of neonatal sepsis prevented. CUA will present the results as cost per DALY averted. Intervention costs and effects will be extrapolated to the Indian neonatal population. Modelling will be used for the target population, time horizon and the decision context to provide much required information for the policymakers. It would guide further decision for upscaling the intervention, if it is found to be efficacious. If the incremental costs of the intervention can be offset by the gains in terms of effectiveness (ie, DALYs), it may be presented for induction within the ambit of existing governmental programme. Modelled CUA results can be presented as health-adjusted life years saved and savings of the healthcare system by disease prevention. We will calculate the incremental cost-effectiveness ratios as the difference in the costs between the intervention and the comparator divided by the difference in health outcomes.

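### A 95% CI for the ICER cannot be read if the simulated cost or effect differences change sign; net benefit from the same 999 draws can

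*Protocol article*

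**What the plan says.** The Uncertainty analysis section fixes the PSA output: "The results under PSA will be simulated 999 times to report a 95% CI for ICERs". The Outcome measures section defines the ICER as "the difference in the costs between the intervention and the comparator divided by the difference in health outcomes". The same section expects the modelling to show the "potential for incremental costs offsets attributable to prevention of morbidity with the proposed intervention", so a negative incremental cost is foreseen. The Introduction describes an earlier "pilot study that showcased a 21% non-significant decline in morbidity due to neonatal sepsis in the intervention arm".

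On input distributions, the Uncertainty analysis section says "Based on nature of parameter, an appropriate probabilistic distribution will be assigned such as" and then lists "beta distribution for risk and utility parameters, gamma distribution for cost parameters, uniform distribution for demographic parameters, etc".

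The Discussion, in its paragraph on expected outcomes, adds uncertainty ranges for costs and for health outcomes, the ICER itself, and sensitivity and threshold work. The article names no cost-effectiveness plane, net-benefit measure or acceptability curve.

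**The concern.** A percentile interval needs values that can be ranked from worse to better. ICERs can be ranked only while every draw lies in one quadrant where both differences are positive. Three things go wrong outside it.

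- **Opposite outcomes share a sign.** Saving money while averting DALYs gives a negative ratio. So does costing more while losing DALYs.
- **Size does not rank value among cost-saving draws.** Saving Rs 150 with 0.126 DALYs averted gives -150/0.126 = -1,190. Saving the same Rs 150 with half the benefit gives -150/0.063 = -2,381. The worse result has the more negative ICER.
- **The ratio jumps at zero effect.** With a positive incremental cost, a draw just above zero effect goes to the far upper tail, and one just below zero goes to the far lower tail.

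Table 2 names the National Health Mission as the policy user. That reader needs to know how likely the probiotic is to be worth funding at a given threshold. An ICER interval that spans quadrants does not say.

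**Working it through.** The 999 simulations are a design choice with no formula behind them, so there is no plan figure to reproduce. The check asks when the planned interval can be read.

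**Inputs from the protocol article:** n = 3072 per arm (Study details); target reduction 30%, so RR 0.70 (Background); pilot reduction 21%, so RR 0.79, and 30% mortality from neonatal sepsis, used here as case fatality (Introduction); beta for risks and gamma for costs (Uncertainty analysis).

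**Assumptions not in the article:** control sepsis risk 5% (2% and 10% as alternatives); further true RR of 0.90; intervention cost Rs 150 or Rs 1,000 per infant; Rs 20,000 per sepsis episode; 20% coefficient of variation on costs; 28 DALYs per death; case fatality drawn from beta(30, 70). DALYs come only from deaths, with the same case fatality in both arms.

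**Formulas.** Let d = p0 - p1, C = intervention cost, T = cost per episode and f = case fatality.

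- Incremental cost: dC = C - d × T
- DALYs averted: dE = d × f × 28
- ICER = dC/dE

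**Central values at 5% control risk:**

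- RR 0.90, Rs 150: d = 0.005; dC = 150 - 100 = 50; dE = 0.005 × 0.30 × 28 = 0.042; ICER = 1,190.
- RR 0.70, Rs 150: d = 0.015; dC = 150 - 300 = -150; dE = 0.126; ICER = -1,190.
- RR 0.70, Rs 1,000: dC = 1,000 - 300 = 700; dE = 0.126; ICER = 5,556.

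**Chance that the effect has the wrong sign.** z = d / sqrt([p0(1-p0) + p1(1-p1)]/n).

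- RR 0.90: 0.005 / sqrt((0.0475 + 0.042975)/3072) = 0.005/0.00543 = 0.92, so about 18% of draws.
- RR 0.70: 0.015 / sqrt((0.0475 + 0.033775)/3072) = 0.015/0.00514 = 2.92, so about 0.2%.

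**Simulation** (50,000 draws per scenario, beta on each arm's risk). Dominant means dE > 0 and dC < 0; dominated means dE < 0 and dC > 0.

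| Control risk | RR | Rs per infant | Dominant | Dominated | 2.5% to 97.5% of ICER (Rs/DALY) |
|---|---|---|---|---|---|
| 5% | 0.90 | 150 | 32% | 18% | about -36,500 to +36,000 |
| 5% | 0.79 | 150 | 68% | 2% | about -3,200 to +8,000 |
| 5% | 0.70 | 150 | 90% | 0.2% | about -2,600 to +1,350 |
| 5% | 0.70 | 1,000 | 0.1% | 0.1-0.2% | about 1,400 to 23,300 |
| 10% | 0.70 | 1,000 | 7% | 0% | about -455 to 6,000 |
| 2% | 0.79 | 1,000 | 0% | 11% | about -228,000 to +289,000 |

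In the first row half the ICERs are negative, with opposite meanings, and the upper limit moves between about 33,000 and 36,000 from run to run. In the third row the intervention meets its target and is mostly cost-saving, yet the interval straddles zero and its negative part does not rank value. In the fourth row the planned interval works.

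**Why net benefit avoids this.** For willingness-to-pay λ, net benefit is NB = λ × dE - dC. The beneficial draw above (dE = 0.126, dC = -150) gives 0.126λ + 150, which is positive for every λ > 0. A harmful draw with d = -0.005 has dC = 150 + 100 = 250 and dE = -0.042. Its ICER is -5,952, and its NB is -0.042λ - 250, which is negative for every λ > 0. The ICER gives both a negative sign; NB separates them.

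**The case against.** **The problem may never occur.** Policy use is tied to the intervention proving efficacious, and this trial is larger than the pilot, so the pilot's non-significance is weak evidence about the trial's precision. At RR 0.70 the wrong-sign share is 0.2% or less at 5-10% control risk. No product price is given, and delivery and supervision costs will be added to it. This stands, and it makes the point conditional. It does not remove it: the summary is chosen before the result is known, and at RR 0.70 cost savings alone can still push most ICERs below zero.

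**Other outputs are promised.** Separate ranges for cost and for outcome would reveal a change of sign. That is true, but they are marginal and do not show how the two move together. Planes and acceptability curves are details an article may leave to a fuller plan. Here, however, the article does not stay silent; it names the interval to be reported.

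**Stronger readings a reader might infer.**

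- *That the plan's beta distribution rules out harm.* A beta placed on a relative risk would do so, because it cannot exceed 1. The article assigns a "beta distribution for risk and utility parameters", offers it as an example chosen by the nature of the parameter, and never mentions a relative risk. A beta on each arm's absolute risk is a natural reading and allowed harm in the simulation above.
- *That 1-18% of draws would show more deaths on the probiotic even at a true 30% reduction.* That range treats deaths as estimated directly in each arm, with assumed case fatality of 10-30%. The Decision model and Effectiveness assessment sections build DALYs from sepsis averted, so the precision of the sepsis comparison is what matters.

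**Conclusion.** The point holds in conditional form. The plan commits to an uncertainty summary that is readable only if nearly all draws show positive cost and positive benefit. It fails with a weak effect or near cost neutrality, which is where a funder most needs guidance. Across the scenarios shown, negative ICERs range from about 0.2% of draws (5% control risk, RR 0.70, Rs 1,000) to about 90% (same risk and RR, Rs 150). The sizes rest on the assumed control risk, costs and DALYs per death; the ordering failure does not.

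The documents do not support saying that the plan excludes harm through its beta distribution. At most, it is worth clarifying how the treatment effect enters the PSA.

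**What to change.** In the Uncertainty analysis section, replace the 95% CI for the ICER with:

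1. the point ICER;
2. the cost-effectiveness plane, with the share of draws in each quadrant;
3. incremental net monetary benefit with a 95% interval, and the probability of being cost-effective (acceptability curve), over a stated willingness-to-pay range.

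All of this comes from the same 999 draws. The cost is a few spreadsheet columns and the need to state a threshold range in advance.

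Add one sentence saying whether the treatment effect is sampled as a beta on each arm's risk or as a log-normal relative risk; both allow harm.

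An infant-level bootstrap of cost and effect is not recommended. Out-of-pocket costs are collected on only 1998 of 6144 infants (about 33%), and treatment costs come from a national costing database and the literature.
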